**Fig. 1 Fig1:**
[figure not shown]
Gantt-Chart showing phases of the study

KTx 360° consists of the following interventions and treatment modules:

### Video consultations

In addition to regular outpatient consultations, video consultations will take place in cooperation between the transplant center and the (pediatric) nephrologist in private practice reducing the number of appointments at the transplant center. At the time of the patient’s appointment at the nephrologist’s office, an experienced physician from the transplant center will be connected to the nephrologist’s office via video platform. Treatment consequences can be discussed together during the session. In case of unexpected medical problems, unscheduled video consultations are possible.

### Psychosomatic-psychosocial risk assessments and adherence coaching via video chat or face-to-face consultations

Even though adherence to immunosuppressants (IS) is crucial to prevent allograft failures, a substantial proportion of transplant recipients are non-adherent to their IS regimen. Among renal transplant patients on average 35.6% of patients per year have been reported to be non-adherent to IS medication [3, 4]. After KTx it is not sufficient to only take the prescribed IS; the timing of IS intake is equally important. Even minor deviations from the prescribed regimen are associated with a higher risk of graft loss. Poor adherence to IS treatment is still the leading preventable cause of graft loss [6].

In our program, each patient will repeatedly receive psychological adherence assessments to screen for non-adherence to IS and to diagnose specific non-adherence phenotypes or patterns. Early in the post-transplant period we will begin with four assessments during the first year and two assessments in the following years. Non-adherence can occur early after transplantation and has been shown to increase over time. Thus, early and continued assessments and interventions after transplantation are considered necessary.

Adherence will be assessed in personal interviews using the Basel Assessment of Adherence with Immunosuppressive Medication Scale (BAASIS©) [7]. A collaborative rather than confrontational interview style will be used in order to elicit honest replies and to avoid social desirability. Non-adherent behaviors broadly fall into two categories: unintentional and intentional nonadherence. Thus, we will assess the following potential barriers of adherence using established instruments: cognitive dysfunctions, lack of resources, lack of knowledge regarding IS, experience of adverse events, mental disorders, psychological distress, low quality of life, and low social support. Finally, applying the necessity-concerns-framework the patients’ personal beliefs about the necessity of their IS medication and their concerns about taking them will be assessed [8].

Depending on the results of the adherence assessments, the psychosocial team will make different recommendations. A patient in need of more information about IS will be referred to an educational group offered by the case managers. It is well known that repetitive teaching is necessary to ensure long-term adherence [9]. Patients can also be referred to a psychologist within the psychosocial team who will offer up to eight treatment sessions per year without waiting period. This intervention can be conducted face-to-face or via video and will deal with psychosocial correlates of non-adherence (e.g., social or work problems, psychological distress) and offer behavioral interventions. If necessary, patients will be referred to more intensive regular care outside the program.

### Cardiovascular assessment and sports therapy via video chat and face-to-face consultations

Exercise capacity after KTx is reduced to 50–70% of normal values [10]. Reasons for reduced physical capacity after KTx are a long period of inactivity during chronic renal failure, side effects of IS such as atrophy of skeletal muscles and osteoporosis, reduced cardiovascular and endothelial function, and lack of long-term rehabilitation programs [11, 12]. Randomized studies have shown that exercise training programs significantly improve maximum oxygen consumption, quality of life, cardiovascular risk, blood pressure, endothelial function and osteoporosis in patients after solid organ transplantation [10, 13, 14]. The magnitude of exercise training effects depends on the duration and the type of the exercise training program.

After KTx in our center, patients usually perform inpatient rehabilitation for 3 weeks directly after hospital discharge. Despite the impressive effects of exercise training in transplant recipients no further intervention to improve daily life activities and physical function are established in long-term rehabilitation in Germany.

Exercise recommendations in transplant recipients include endurance training 2–4 times per week (improving vascular function, reduced cardiovascular risk) and regular resistance training (to prevent osteoporosis and skeletal muscle loss) [15]. In KTx360° a regular home based exercise training program will be implemented. Initiated 2–3 months after transplantation patients (including criteria are duration of dialysis longer than 3 years, coronary artery disease, diabetes mellitus, BMI > 35, patients under the age of 18 years) will perform a physical examination and an incremental exercise testing on an ergometer including blood lactate measurements for determination of cardiovascular and skeletal muscle function. Furthermore, a 30 min constant load test on a cycle ergometer with ECG, blood pressure, blood lactate and glucose monitoring, a Timed up and go test, a Sit-to-Stand-test and measurement of steps per day will be performed initially and every 12 months for evaluation of secondary outcome parameters. Exercise training recommendations are derived from exercise intervention studies with heart and renal transplant patients and include moderate endurance training or moderate resistance training every other day:Exercise capacity near to normal (>80% of normal values): Initial duration 15-30 min with 35–60% of maximum exercise capacity.Exercise capacity reduced (60–80% of normal values): Initial duration 10-20 min with 30–50% of maximum exercise capacity.Exercise capacity reduced (<60% of normal values): Initial duration 15-20 min with 25–40% of maximum exercise capacity.

Exercise training will be monitored by an exercise physiologist via a wearable system to measure physical activities and the respective heart rates. A regular feed–back, based on continuous training data interpretation, will be given monthly by video/phone conference in order to motivate the patient and adapt the training prescriptions. In the first year after KTx patients will be seen 4 times face-to-face (2 times a year thereafter), and during these occasions patients will be monitored during a 30 min endurance exercise training.

### Case management and coordination of post-transplant care/quality management

In the participating transplant centers, a coordination office will be established. Case managers will coordinate post-transplant care individually and offer continuous support to patients. The case managers will have the following tasks: individual organization of post-transplant care including scheduling of follow-up appointments, medical information management, updating the internet-based case file, liaising with regional care partners, organization of regular care outside the program, and preparation as well as coordination of case conferences. Another central task is organization and support of transition from pediatric into adult care. The case management will also organize weekly case conferences (nephrologists, pediatric nephrologists, sports medicine specialists, psychologists, case managers) within the transplant centers and yearly quality circles of all program participants to discuss and decide on standard operating procedures to be followed by all participating care givers.

### Internet-based case file and video consultation platform

The internet-based case-file platform that is based on a customized version of the program “Case Plus®”, provided by the company Symeda GmbH, will be used for documentation of all relevant medical data. In addition, the patient can include daily updates on his/her health status in the internet-based case file. Lab values and other important patient data will regularly be included in the internet-based case file by the case managers, the private practice nephrologists and/or by automatic interfaces to hospital and office software. The internet-based case file will be used for coordinating post-transplant care, documenting patient contacts and utilizing the treatment modules of KTx360°. Data can be exported from the case file and pseudonymized for evaluation purposes. Most of the entries in the internet-based case file can be accessed by the patients at any time.

### Goals

The main goals of KTx360° are an improvement of graft survival and quality of life after kidney transplantation and a reduction of health care costs caused by avoidable hospital treatments due to complications or co-morbidities.

To achieve these goals, sustainable efforts to reduce cardiovascular risks and immunological risks, to increase adherence to medication and scheduled visits, and to enhance care in the transition phase have been implemented in KTx360°. Thereby, we expect to reduce health care costs by reducing the frequency of hospitalizations and by postponing the need for dialysis following graft loss. Due to an individualized psychosocial care, an improvement in quality of life can be expected.

### Study endpoints

The primary endpoint of the study will be the 20% reduction in health care costs due to a reduction of hospital utilization of study participants as compared to the control groups (endpoint 3).Increase of adherence for outpatient visits. Goal: Participation in 90% of scheduled visits.Increase of adherence to immunosuppressive therapy. Goals: 1) Coefficient of variation of levels of immunosuppressants <0.4 in 75% of patients. 2) Non-adherence in BAASIS-interview <10% in incident and <20% in prevalent patients / year.Reduction of transplant-associated complications. Goals: 1) Reduction of hospitalization costs by 20% as compared to a control group (primary endpoint) 2) Reduction of graft losses by 25% as compared to a control group.Improvement of cardiovascular fitness and stabilization of weight. Goals: 1) Reduction of hospitalizations caused by cardiovascular complications by 25% as compared to a control sample. 2) Stable weight (weight ± 5%) in patients with a baseline Body Mass Index >18.5 kg/m^2^
Quality of life of the participants will significantly improve. Goals: 1) In the mental subscale of SF-12, 80% of the participants will achieve results that do not differ from norms for the general population. 2) In the physical subscale, 20% will reach results comparable to the general population.Establishment of Standard Operating Procedures (SOPs) including all sectors of the German healthcare system. Finalization of SOPs within 48 weeks of study start.Implementation of an internet-based case file including all sectors of care. Goal: 75% of patients will have used the internet-based case file after 12 months of study start.Implementation and acceptance of telemedicine visits. Goal: 80% of participating physicians will use a telemedicine visit at least once in 80% of their patients within 12 months.

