## Methods/design

Inclusion criteria for this study are: KTx from 2010 to 2019 that was performed at one of the two kidney transplantation centres in the German state of Lower Saxony, study participation of the (pediatric) nephrologist responsible for the patient’s follow-up, and membership of the patient in a participating statutory health insurance. Patients of all ages can be included.

Two cohorts of patients will be included in KTx360°: incident and prevalent patients. Incident patients will have their kidney transplantation during the recruitment period of the study (2017 to 2019) at one of the two transplant centers in Lower Saxony. There are about 225 kidney transplantations per year in these centers (210 adults and 15 children/adolescents). Assuming a response rate of 80% caused by non-participation of health insurances, private practice nephrologists or patients who decline participation, we expect to include a total sample of *n* = 487 (*n* = 448 adults, *n* = 39 children/ adolescents) incident patients during the 31 months recruitment period. With a rolling recruitment process and an assumed 15% drop-out rate per year due to graft loss, death or withdrawal from the study we expect to obtain data from 286 adults and 26 children/adolescents completing 2 years post-transplant observation and of 121 adults and 12 children/adolescents with three post-transplant years. Prevalent patients who had their kidney transplantation between 2010 and 2016 will be included in the study when they attend their regular follow-up care visits at the transplant centers. Under similar conditions as the incident patients and an assumed 5% mortality rate per year for adults before study inclusion, we expect a total of *n* = 1046 prevalent patients (*n* = 83 children/adolescents) to participate in the study.

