### Evaluation and study analyses

The endpoints will be evaluated by an external independent research institute (IGES Institute GmbH). The study design is a combination of a recurrent institutional cycle design and a multiple time-series design with a non-equivalent control group allowing minimizing bias because of the non-randomized research design of the study [16]. Evaluation will comprise an outcome evaluation for endpoints 1 to 5 and a process evaluation for endpoints 6 to 8 in accordance with the guidelines of the Medical Research Council [17, 18].

The evaluation will use different sources of data: claims data from the statutory health insurances, data assessed during the study on patients’ health, adherence and quality of life as well as data from documentation and process evaluation. Goal 1 (increase of adherence to scheduled follow-up visits) will be evaluated with data from the internet-based case file and with claims data on number of follow-up care visits at the private practice nephrologists and the transplant centers respectively. For Goal 2 (increase of adherence to IS therapy) the evaluation will use IS trough and target levels from the internet-based case file and the BAASIS interview as conducted in the psychosomatic assessments. Goal 3 (reduction of transplant-associated complications) can be evaluated with claims data on hospital utilization and costs as well as on graft loss. The cardiovascular fitness of the patients (Goal 4) will be evaluated with claims data on hospitalizations due to cardiovascular events, with participation rates in training programs as documented in the internet-based case files and with data from the cardiovascular assessments on BMI and on fitness indicators (lactate, heart rate and blood pressure as well as subjective burden). For the evaluation of goal 5 (improvement of quality of life), health-related quality of life measures as assessed in the psychosomatic module will be used. For goals 6 to 8 (implementation and acceptance of SOPs, internet-based case files, telemedicine treatments), data from study documentation on implementation of SOPs, on the internet-based case file and on the telemedicine treatments will be used. In addition, patients as well as private practice nephrologists and nephrologists at the transplantation centers will take part in yearly process evaluations to assess acceptance of all aspects of the program.

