To evaluate the goals longitudinal and cross-sectional analytic procedures are used. In both, comparisons between the included patients and the control groups are conducted if applicable. Longitudinal analyses will be conducted with regression analyses in mixed models with repeated measures. This approach is feasible to estimate within-person change over time and group differences in within-person change over time. Cross-sectional group comparisons will be analyzed with regression models without repeated measures. All models will be adjusted for possible confounders, such as age of patients, distance to transplant center or co-morbidities. Descriptive statistics will be conducted to illustrate results, achievement of endpoints (see section on endpoints) and sample characteristics. All effects will be tested with a significance level of *p* = .05.

Group differences in within-person change and levels at one point in time will be evaluated with data available for the comparison groups (mainly data from statutory health insurances). For example, in year one after transplantation costs for hospitalizations of incident patients who received their transplantation in 2017 are expected to be lower as compared to the historical comparison group (prevalent patients with transplantation between 2010 and 2016) and as compared to the external control group (with transplantation in 2017 at different transplant centres). Additionally, data on adherence assessed with the BAASIS interview of prevalent patients who are included in the study 12 months after transplantation can be compared to the adherence scores of incident patients in month 12 after transplantation.

For data of the psychosomatic and cardiovascular assessments, the evaluation of process and health status are assessed in regular visits of the participating incident and prevalent patients: Within-person change after transplantation will be analyzed. For example, we would expect positive changes in quality of life in incident and prevalent patients during the study period. We would also expect an increase in usage and acceptability of telemedicine treatments among the nephrologists.

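### The ±5% stable-weight goal has no age limit, so a child who simply grows taller can be counted as not meeting it

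*Protocol article*

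**What the plan says.** Under Study endpoints, endpoint 4 is headed "Improvement of cardiovascular fitness and stabilization of weight". Its second goal reads "Stable weight (weight ± 5%) in patients with a baseline Body Mass Index >18.5" kg/m². The rule applies equally to gain and loss, has a lower BMI bound only, and mentions no age.

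The population is not limited to adults. Methods/design states "Patients of all ages can be included" and expects 39 children and adolescents among 487 incident patients and 83 among 1,046 prevalent patients. Of the incident children, 26 are expected to complete two post-transplant years and 12 to complete three.

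The section on cardiovascular assessment and sports therapy opens its list of entry criteria with more than three years on dialysis and continues "coronary artery disease, diabetes mellitus, BMI > 35, patients under the age of 18 years". Evaluation and study analyses says that goal 4 will be evaluated, among other sources, "with data from the cardiovascular assessments on BMI and on fitness indicators", and that "Descriptive statistics will be conducted to illustrate results, achievement of endpoints (see section on endpoints) and sample characteristics". None of these sections gives a separate scoring rule for children.

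**The concern.** In an adult, height is effectively fixed, so percent change in weight and percent change in BMI are the same thing, and a ±5% band is a workable definition of stability. In a growing child they differ: weight must rise if body proportions are to stay the same. A rule that requires weight to stay within 5% therefore counts expected growth as a departure from the goal. A fixed BMI threshold of 18.5 without reference to age is also a poor way to choose which children the goal covers.

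What is at stake is the meaning of one reported proportion. If children are pooled with adults, the share with stable weight is lowered by growth, which is unrelated to the programme. If children are shown separately, their figure mainly reflects how much they grew. In both cases the rule, followed as written, gives a wrong classification.

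**Working it through.** The article gives no figure for this goal (no expected proportion, sample size or power), so there is nothing of its own to reproduce. The check is arithmetic on the band.

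**Inputs from the article**
- Band: ±5% of weight, baseline BMI above 18.5 (Study endpoints).
- Children and adolescents: 39 incident and 83 prevalent (Methods/design).
- All participants: 487 incident + 1,046 prevalent = 1,533 (Methods/design).
- Observation of incident patients: two to three post-transplant years (Methods/design).

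**Step 1. Adult, constant height.** Weight = BMI × height², so weight ±5% equals BMI ±5%. At BMI 25 the band runs from 25 × 0.95 = 23.75 to 25 × 1.05 = 26.25. The rule behaves as intended.

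**Step 2. Child, constant BMI.** The ratio of later to baseline weight is (later height / baseline height)². The upper limit is crossed when this exceeds 1.05, that is, when height grows by more than √1.05 − 1 = 0.0247, or 2.47%.

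| Baseline height | Growth that reaches +5% weight | Per year over 2 years | Per year over 3 years |
|---|---|---|---|
| 130 cm | 3.2 cm | 1.6 cm | 1.1 cm |
| 140 cm | 3.5 cm | 1.7 cm | 1.2 cm |
| 150 cm | 3.7 cm | 1.9 cm | 1.2 cm |
| 160 cm | 4.0 cm | 2.0 cm | 1.3 cm |

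**Step 3. Worked case.** A child of 150 cm with BMI 19 weighs 19 × 1.50² = 42.75 kg. At 154 cm and the same BMI the weight is 19 × 1.54² = 45.06 kg. The change is 45.06 / 42.75 − 1 = +5.4%, so the goal is missed although BMI has not moved.

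**Step 4. If BMI also rises with age.** The weight ratio is then (BMI ratio) × (height ratio)². With an assumed BMI rise of 2%, the height growth that reaches the limit falls to √(1.05 / 1.02) − 1 = 1.46%, or 2.2 cm at 150 cm. Constant BMI is therefore the lenient case.

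**Step 5. Ceiling on the number affected.** 39 + 83 = 122 children, and 122 / 1,533 = 8.0%. By cohort this is 39 / 487 = 8.0% and 83 / 1,046 = 7.9%. It is a maximum for two reasons: children with baseline BMI of 18.5 or below are outside the goal and their number is not given, and adolescents who have stopped growing are not affected by the height argument.

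**The case against.** **Status of the goal.** It is secondary. Unlike the goals for adherence and quality of life, it carries no target proportion, so no pass mark is shifted, and its achievement is reported descriptively. That stands, and it limits the weight of the point.

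**BMI as data source.** The evaluation section names BMI among the data for goal 4, and the assessment data are also analysed as within-person change, so the direction of change may be visible outside the ±5% score. This helps in part. Scoring BMI would shrink the height effect, but raw BMI is not standardised for age, and the endpoint itself is defined on weight. Adjusting a model for age does not alter how an individual child is classified.

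**Condensed article.** A paediatric rule may exist in a fuller document. However, the article does not leave the definition open: it states a band and an eligible set, and that set includes children.

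**A stronger reading.** A reader might infer that the rule is equally wrong for very obese adults, because a patient with BMI above 35 who loses 6% misses the goal while one who gains 4.9% meets it. That is how the rule scores them, but the documents do not support calling it an error. The stated aim is stabilization, for which a two-sided band is the natural measure. The exercise section does not name weight loss as an aim. BMI above 35 is one of five entry criteria, not the module's defining target. Cardiovascular benefit is assessed by other measures, namely cardiovascular hospitalizations and fitness indicators. Weight loss after transplantation can also reflect illness, so counting it as unstable is defensible. The article gives no figures from which the number of such adults could be estimated.

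**Conclusion.** The point holds for patients under 18. As written, the goal applies a weight band suited to adults to growing children, and height growth of about 2.5% is enough to miss it. Nothing elsewhere in the article overrides the definition.

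The size is at most 122 of 1,533 participants (8.0%); the true number is smaller by an amount that the article does not allow one to compute. It would be wrong to read the 122 as children who will be misclassified.

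The conclusion rests on three assumptions:
- Growth exceeds the rates in the table, roughly 1 to 2 cm a year over two to three years. The article gives no growth data.
- The comparison runs from baseline over the observation period.
- The article's counts of children and adolescents approximate the under-18 group. It does not state the age limit behind those counts.

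This is a definition worth correcting, with limited consequences. The primary endpoint (hospitalization costs) and its power calculation do not depend on it.

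**What to change.** - Restrict the ±5% weight goal and its BMI cut-off of 18.5 to patients aged 18 or over at baseline.
- For patients under 18 at baseline, report change in age- and sex-specific BMI z-score separately, naming the reference population. This also brings in the children whom the 18.5 cut-off now leaves out.
- State whether the adult goal is scored on weight or on BMI, so that the endpoint and evaluation sections agree.
- Keep the two-sided band for adults as the measure of stabilization. Showing gains and losses beyond 5% separately would be informative but is optional, and corrects no error.

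The cost is small. The z-score needs weight, height, age and sex; BMI data are already planned, but in children height must be measured at each assessment and not carried forward. The denominator of the ±5% proportion falls by at most 122, leaving up to 1,533 − 122 = 1,411 adults before the BMI cut-off is applied. The children's result becomes a continuous summary, not a stable/not-stable proportion, so the two age groups no longer share one headline figure.
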